## Objectives {7}

Our trial aims to test two main hypotheses:

H1: Participants in the villages allocated to the stand-alone Home Gardening Intervention will experience significantly improved food security at the 12-month endpoint, compared to participants in the control group.

H2: Participants receiving SH + in combination with HGI will exhibit superior food security outcomes compared to those receiving HGI alone.

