## Trial design {8}

The 30 participating villages within the Nakivale refugee settlement will be the unit of randomization and will be assigned to one of three arms: (1) Enhanced Usual Care (EUC), (2) Home Gardening Intervention (HGI) or (3) a combined Self-Help Plus and Home Gardening Intervention (SH + HGI). To account for baseline differences associated with settlement patterns of recent arrivals, the randomization will be stratified and staggered, with villages allocated in three phases (see section on Participant timeline {13} for details). The trial is designed to demonstrate the superiority of HGI, and particularly SH + HGI, compared to EUC in improving food security outcomes at 12 months post-intervention. The cluster-randomized controlled trial (cRCT) design is essential due to the nature of the interventions, which are delivered at the community level, and to minimize the risk of contamination between the intervention groups that could arise from individual randomization within the same village.

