## Interventions

### Explanation for the choice of comparators {6b}

This study employs a three-arm design to evaluate the effectiveness of a Home Gardening Intervention (HGI) alone and in combination with a mental health intervention (SH +). The Enhanced Usual Care (EUC) arm serves as a control, providing a benchmark for comparison while offering a higher level of support than a simple waitlist condition, thus mitigating potential nocebo effects. Participants in the EUC arm will also receive the HGI training and materials after the final 12-month data collection time point, ensuring they are not disadvantaged by participating in the control group. The HGI arm is designed to assess the impact of climate-smart agricultural practices on food security. The combined SH + HGI arm allows us to test the hypothesis that addressing mental health can enhance the effectiveness of agricultural interventions in this refugee population. This design allows for a direct comparison between the interventions and the control, as well as an assessment of the potential added value of integrating mental health support with agricultural training.

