## Statistical methods

### Statistical methods for primary and secondary outcomes {20a}

For the primary analysis, the results will be based on an intention-to-treat (ITT) approach, using the initial randomization of the intervention arms. Secondary analyses will employ a per-protocol approach, including only participants who completed the allocated intervention as planned. Analyses will focus on the primary outcome of food insecurity and the secondary outcomes of household dietary diversity, child malnutrition and maternal psychological distress at the 12-month endpoint. Maternal psychological distress measured at 3 months will serve as a manipulation check to verify that SH + was effective. Analyses will be conducted at the individual level, comparing the change from baseline to follow-up between arms, adjusting for clustering and baseline score.

The preliminary analysis will compare participant sociodemographic characteristics and outcome variables across the three intervention arms at baseline. Hierarchical models will be used to examine differential effects of intervention arms on outcomes. Assuming a parametric approach, we will employ models with random effects to account for clustering at the village level and repeated measures within participants. The fixed effects included in the models will be (1) intervention, represented by two indicator variables; (2) time, measured at baseline, 3-month follow-up and 12-month follow-up; and (3) the interaction between intervention and time. Fixed effects parameters will be tested with the Wald test (*t* test, *p* < 0.05, two-sided) and 95% confidence intervals without adjustment for multiple comparisons for the global test of treatment effects. A significant interaction of intervention and time suggests differential intervention effects and will be followed by pairwise comparisons to test the primary hypotheses: the EUC group vs. the HGI group, and the HGI group vs. the SH + HGI group. Participants’ demographic characteristics, baseline levels of primary and secondary outcomes and our village stratification variable (accounting for the settlement patterns of recent arrivals) will be included as covariates in the analyses.

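### SH+HGI versus EUC, the comparison the design statement stresses, is not named among the tests of the primary hypotheses

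*Protocol article*

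**What the plan says.** Four sections of the protocol article bear on which arms are compared.

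- **Trial design {8}:** "The trial is designed to demonstrate the superiority of HGI, and particularly SH + HGI, compared to EUC".
- **Explanation for the choice of comparators {6b}:** "This design allows for a direct comparison between the interventions and the control, as well as an assessment of the potential added value" of adding mental health support. The plural covers both active arms against control.
- **Objectives {7}:** two hypotheses. H1 is that HGI participants "will experience significantly improved food security at the 12-month endpoint, compared to participants in the control group". H2 is that SH+HGI participants "will exhibit superior food security outcomes compared to those receiving HGI alone".
- **Statistical methods {20a}:** "A significant interaction of intervention and time suggests differential intervention effects and will be followed by pairwise comparisons". These are the tests of the primary hypotheses, and they are listed as "the EUC group vs. the HGI group, and the HGI group vs. the" SH+HGI group.

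The same section codes intervention by two indicator variables and applies Wald tests to the fixed effects at two-sided 0.05. It does not say which arm is the reference. Sample size {14} powers a between-arm difference without naming the pair.

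**The concern.** The first two sections promise SH+HGI against EUC, and the first stresses it. The last two give a closed list of hypotheses and pairwise tests that leaves it out. This is not detail deferred to an analysis plan, because the protocol enumerates its pairwise tests and the list does not match its own design statement.

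If both components help, SH+HGI versus EUC is the largest expected difference in the trial. A modest benefit from each can leave one or both adjacent tests non-significant while the package as a whole clearly differs from control. The claim in the design statement would then rest on a contrast that nobody had named in advance. Added after the results are known, it would be post hoc.

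**Working it through.** **1. Reproduce the plan's figure.** Inputs from Sample size {14} and the abstract: 10 villages per arm, so J = 20 for a pair of arms and P = 0.5; 30 dyads per village less 20% attrition, so n = 24; ICC 0.01; 50% of variance explained at individual level and 20% at cluster level; two-sided alpha 0.05; power 95%.

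SE² = ICC(1 − R²_cluster)/[P(1−P)J] + (1 − ICC)(1 − R²_indiv)/[P(1−P)Jn]

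= 0.01 × 0.8/5 + 0.99 × 0.5/120 = 0.0016 + 0.004125 = 0.005725, so SE = 0.0757 SD.

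Detectable difference = (t for 0.975 + t for 0.95) × SE. With 17 df (one cluster-level covariate) this is (2.110 + 1.740) × 0.0757 = 0.291. With 18 df it is 0.290. The stated 0.291 SD is therefore a two-arm comparison. Since the arms are equal in size, it applies to any of the three pairs.

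**2. When the omission matters.** In one model the two adjacent estimates sum exactly to SH+HGI minus EUC. If both planned tests succeed in the beneficial direction at 24 df, each exceeds 2.064 SE. Their sum then exceeds 2 × 2.064 = 4.13 SE, and since all three contrasts have the same SE, SH+HGI versus EUC is significant too. The gap is confined to trials where at least one planned test fails.

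**3. How often that happens.** The protocol does not say how the benefit divides between the two steps, so the splits below are assumptions. Three arm means were simulated with SE 0.0757 per pairwise contrast and 24 df. Thirty villages less three arms would give 27 df, which changes the results by about 1 point. Missed means that a 2-df joint test of the 12-month arm differences and SH+HGI versus EUC are both significant while neither planned test is.

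| EUC to HGI / HGI to SH+HGI (SD) | Power H1 | Power H2 | Both | SH+HGI vs EUC | Missed |
|---|---|---|---|---|---|
| 0.10 / 0.10 | 25% | 25% | 3% | 72% | 17% |
| 0.15 / 0.15 | 48% | 48% | 17% | 97% | 14% |
| 0.20 / 0.10 | 72% | 25% | 13% | 97% | 11% |
| 0.20 / 0.20 | 72% | 72% | 48% | over 99% | 4% |

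At 0.15/0.15:

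- SH+HGI versus EUC keeps 92% power after the joint test.
- At least one planned test fails in 100% − 17% = 83% of trials.
- The missed share is 14% with the joint test and 18% without it.

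A second run with 27 df and an even split of the total benefit gives missed shares of 17%, 18%, 15%, 8% and 3% for totals of 0.20, 0.25, 0.291, 0.35 and 0.40 SD.

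**The case against.** The analysis matches the hypotheses. Objectives {7} asks whether HGI works and whether SH+ adds to it, and Statistical methods {20a} tests exactly those two questions. On this view the outlier is one sentence under Trial design {8}, with loose support under {6b}, and rewording would remove the conflict with no change to the analysis. That stands as an alternative repair, but some action is needed either way.

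A reader might go further and infer that the combined arm is never tested against control and that the trial could produce no formal result for it. The documents do not support this. The fixed effects are Wald-tested with confidence intervals, and if EUC is the reference arm, as is usual for a control, the SH+HGI coefficient at 12 months is this contrast. What remains is that the reference arm is not stated and that the coefficient is not tied to a hypothesis. The global interaction test also involves the combined arm, but it does not show which arms differ.

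Nor is it right that the two adjacent results cannot add up to the third: the estimates do, exactly, and two successes imply it.

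Finally, the size of the problem depends on an assumed split. If HGI alone delivered the full 0.291 SD, H1 would have its stated 95% power and little would be lost.

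**Conclusion.** The concern holds as a mismatch between the stated aim and the named tests. The comparison that Trial design {8} stresses has no named, prespecified confirmatory test, and whether the model reports it depends on a reference arm that the protocol does not give. The planned tests of H1 and H2 remain valid.

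The consequence is moderate. With benefit spread over both steps, the package would beat control with neither planned test significant in roughly 4% to 17% of trials over the splits tabulated, and in about 14% at 0.15 SD per step. These shares rest on the protocol's own ICC, explained variance and attrition, on the assumed splits and degrees of freedom, and on a 12-month joint test that the protocol does not currently specify.

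**What to change.** Name SH+HGI versus EUC on the Food Insecurity Experience Scale at 12 months as a third prespecified pairwise contrast from the same model, state the reference arm, and align Objectives {7}, Trial design {8} and Statistical methods {20a}.

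To hold familywise error at 5%, test the three contrasts each at 5% only after a significant 2-df joint test of the 12-month arm differences. With three arms this is a closed procedure. It must replace the present interaction gate, which spans 3 and 12 months: arm differences at 3 months alone could open that gate, so it does not protect the 12-month tests. A reader might think a third test costs no alpha under the plan as written; that holds only with the new gate.

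The cost is that change of gate and one more confirmatory contrast. No further participants or data are needed, and the arms are equal, so the stated 95% power for 0.291 SD at an unadjusted 0.05 applies to the new contrast before gating. Trial status reports baseline collection still under way at submission, so the change could be made before outcome data exist.

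If the sponsor does not want the contrast, Trial design {8} and the comparator rationale {6b} should be reworded so that they no longer claim it.

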### Interim analyses {21b}

No interim analyses are planned.

### Methods for additional analyses (e.g. subgroup analyses) {20b}

Subgroup analyses will be conducted to explore moderation effects of initial food insecurity and psychological distress at baseline, exposure to trauma, cultural differences (tribal and national identity), pre-existing adaptive capacity (e.g. previous farming experience) and length of stay in the camp. These will be examined by including interaction terms (intervention × moderator variable).

### Methods in analysis to handle protocol non-adherence and any statistical methods to handle missing data {20c}

The primary analysis will be based on an intention-to-treat (ITT) approach. A per-protocol analysis will be conducted as a secondary analysis. Missing data will be handled using imputation estimation methods (maximum likelihood, K-Nearest Neighbors) estimation if missing at random. We will utilize a conservative last-observation-carried-forward (LOCF) approach for missing follow-up data among completers.

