### Sample size {14}

The sample size calculation was conducted using *PowerUp* [60]*!* and was based on the primary outcome of food insecurity. A total sample size of 900 mother–child dyads (300 per arm) is required to detect a between-arm difference in the primary outcome of 0.291 standard deviations with 95% power and an alpha of 0.05. This calculation assumes an intra-cluster correlation coefficient (ICC) of 0.01, based on previous studies in similar settings [61, 62], and accounts for 50% of the variance being explained by individual-level covariates and 20% by cluster-level characteristics. The calculation also assumes a conservative 20% attrition rate at the 12-month follow-up.

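### K-Nearest Neighbors stands beside maximum likelihood with no rule for choosing; if it fills missing 12-month FIES, the Wald test is too liberal or the effect is shrunk

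*Protocol article*

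**What the plan says.** Section {20c} of the protocol article makes intention-to-treat primary and then gives two rules for missing data. The first covers data missing at random: "Missing data will be handled using imputation estimation methods (maximum likelihood, K-Nearest Neighbors) estimation if missing at random". The second is: "We will utilize a conservative last-observation-carried-forward (LOCF) approach for missing follow-up data among completers". Neither rule is tied to particular variables. Nothing says which one feeds the primary analysis, how neighbours are chosen, or how the uncertainty of a filled-in value reaches the standard error.

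Section {20a} describes the model: "we will employ models with random effects to account for clustering at the village level and repeated measures within participants". It describes the test: "Fixed effects parameters will be tested with the Wald test (*t* test, *p* < 0.05, two-sided) and 95% confidence intervals". A significant intervention-by-time interaction opens the two primary comparisons: "the EUC group vs. the HGI group, and the HGI group vs. the SH + HGI group".

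The Sample size section {14} states: "The calculation also assumes a conservative 20% attrition rate at the 12-month follow-up".

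**The concern.** The bracket in {20c} lists two methods as equals, although they behave differently under the test in {20a}. Likelihood estimation in the mixed model uses each observed visit and creates no values. K-Nearest Neighbors is a single imputation: a missing score becomes the score of one similar mother, or the average of several, and the model then counts it as data.

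What follows depends on who may serve as a neighbour.

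- **Arm used in matching:** the filled-in values repeat information already in that arm. The reported standard error is too small.
- **Arm ignored:** mothers in other arms supply part of each arm's values. The arm difference is pulled toward zero.

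If this method supplied the 12-month FIES, the tests behind H1 and H2 would have either a type I error above the stated 5% or an attenuated effect. Which of the two occurred would turn on a choice that the article leaves open.

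**Working it through.** **Inputs from the protocol article.** 30 villages, 10 per arm, 30 dyads each; ICC 0.01; 50% of variance explained at individual level and 20% at cluster level; 20% attrition; two-sided alpha 0.05; 95% power. A pairwise contrast uses J = 20 villages with P = 0.5.

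**Step 1: the plan's own figure.** The article says that 900 dyads "is required to detect a between-arm difference in the primary outcome of 0.291 standard deviations with 95% power and an alpha of 0.05". The two-level formula is

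MDES = (t[0.975, df] + t[0.95, df]) × √( ICC(1 − R²c)/(P(1−P)J) + (1 − ICC)(1 − R²i)/(P(1−P)Jn) ).

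- With n = 30 × 0.8 = 24: √(0.01×0.8/5 + 0.99×0.5/120) = √(0.0016 + 0.004125) = 0.0757. On 17 df, (2.110 + 1.740) × 0.0757 = 0.2913; on 18 df, 0.2902.
- With n = 30: √(0.0016 + 0.0033) = 0.0700, giving 0.2695 (17 df) or 0.2684 (18 df).

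The stated 0.291 reproduces, and only with 24 observed dyads per village. The design thus pays for attrition, whereas an analysis of filled-in data reports precision as if none had occurred.

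**Step 2: approximate size of the standard-error fault.** Let r = 0.8 be the observed fraction and K the number of neighbours, all from the same arm. Take the complete-data individual-level variance as 1 and leave the small village component aside.

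- True variance of the filled-in mean: 1/r + (1 − r)/K. For K = 5 this is 1.25 + 0.04 = 1.29.
- Variance the model reports: r + (1 − r)/K = 0.80 + 0.04 = 0.84.
- Ratio of reported to true standard error: √(0.84/1.29) = 0.807. On 17 df the implied type I error is 10.7%.

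**Step 3: simulation.** 4,000 trials per setting; 30 × 30; ICC 0.01; covariate R² 0.5; 20% missing at 12 months, at random given baseline score; baseline-adjusted random-intercept model; HGI vs EUC, without the interaction gate. Assumed, because the article is silent: K = 1, 5 or 10, the donor rule, the covariates, the strength of the missingness mechanism and the degrees of freedom.

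| Handling of missing 12-month score | Reported SE / true SE | Type I error, 17 df | 27 df | z | Mean estimate, true 0.291 | Power, t reference |
|---|---|---|---|---|---|---|
| Likelihood on observed values | 1.00 | 3.9% | 4.4% | 5.5% | 0.291 | 94.0–94.5% |
| Neighbours matched with regard to arm | 0.79–0.81 | 9.0–10.2% | 9.9–11.3% | 11.7–13.0% | 0.290–0.291 | not meaningful at inflated error |
| Arm ignored in matching | about 1.00 | 3.7–4.1% | 4.3–4.6% | 5.5% | 0.230 | 88–93% |

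The shrinkage is (0.291 − 0.230)/0.291 = 21%. This is close to the missing fraction, since 0.8 × 0.291 = 0.233.

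**Step 4: sensitivity, neighbours matched with regard to arm.**

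- 10% missing: type I error 6.5–7.4% on a t reference, 8.2–8.6% on z.
- Covariate R² 0.2 with 20% missing: 8.5–9.7% (17 df), 9.6–10.8% (27 df).
- A separate simulation with data missing completely at random and visit correlations of 0.5–0.7 gave 9.2–9.5% (27 df) for K = 5 or 10, and 7–8% for K = 1. With arm ignored, its estimates were 0.233–0.239.

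**Step 5: the gate in {20a}.** The three-visit model was simulated with the interaction test first (1,500 trials per setting, K = 5, same-arm neighbours, 20% missing, visit correlation 0.5 and 0.7). With no effect in any arm:

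- global interaction test: 12.5–13.7%;
- ungated pairwise test: 8.0–9.8%;
- H1 declared after both steps: 4.5–5.0%, against 1.6–2.0% with no missing data.

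**The case against.** The strongest reply is that the article may never intend K-Nearest Neighbors for the outcome. Maximum likelihood comes first in the bracket, and the hierarchical model in {20a} can be fitted by likelihood to all observed visits. K-Nearest Neighbors could be meant for sporadic gaps in covariates, where it does little harm. This stands as far as it goes. A reader might infer that every missing FIES will be filled from neighbours and that the trial therefore runs at about twice its nominal error. The text does not support that. It does not confine the method to covariates either.

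The other objections stand in part.

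- **Carry-forward takes some of the missing follow-up.** It is assigned to completers, so sending the full 20% through K-Nearest Neighbors is an upper case.
- **20% is the article's own cautious figure.** With less attrition the fault is smaller, as the 10% results show.
- **The two faults are alternatives.** It would be wrong to infer inflation and shrinkage together. With arm ignored, error is near nominal and the cost is bias and power.
- **The gate limits false claims.** It is tempting to say that H1 and H2 would each be declared falsely at near 10%. When no arm has an effect, the gated run puts H1 at about 5%. The protection comes from requiring two tests, and the first is itself inflated. By reasoning, not simulation, the protection should fade when one arm truly differs: the gate then tends to open, and the other comparison rests on the pairwise test alone.
- **Donor rules and variance methods belong in an analysis plan.** Their absence from a condensed article is no fault. The point is that the article names, without restriction, a method that its stated test cannot accommodate unadjusted.

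**Conclusion.** The concern holds conditionally. Section {20c} leaves open whether a valid or an invalid method supplies the primary FIES test. If K-Nearest Neighbors is used there without a variance correction, at 20% missing:

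- **Matching with regard to arm:** the reported standard error is about 0.8 of its true size, the ungated pairwise type I error is about 9–11% on a t reference, and the global interaction test is also inflated.
- **Matching that ignores arm:** the error rate holds, the effect falls by about a fifth, and power on a t reference falls by about 1 to 6 points against likelihood estimation (94.0% to between 88.4% and 92.8% on 17 df).

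These sizes rest on the planned attrition, an ICC of 0.01, and assumed values for K, the donor rule, covariate strength and degrees of freedom. The direction of each fault does not depend on those values. Likelihood estimation on the observed records showed neither fault and gave power of 94.0–95.5% across the three references, in line with the planned 95%.

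**What to change.** In {20c}, name one primary method: missing FIES, HDDS, K6 and HAZ are handled by likelihood estimation in the mixed model on all observed visits, with no filled-in outcome values. Remove K-Nearest Neighbors for outcome variables; it may stay for sporadic missing baseline covariates. Carry-forward, if kept, should be labelled a sensitivity analysis so that it does not compete with the primary method.

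If an imputation-based sensitivity analysis is wanted, use multiple imputation done separately by arm. Include village effects and, where the outcome has one, the 3-month value. Combine the results with Rubin's rules.

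The cost is wording only. Standard errors will be wider than those an arm-aware fill-in would report: in the simulation 0.0786 against 0.0637–0.0690, or 14–23% wider (0.0786/0.0690 = 1.14; 0.0786/0.0637 = 1.23). That is their correct size, and the sample size already allows for it.

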## Methods: participants, interventions and outcomes

### Study setting {9}

This study will take place within the Nakivale refugee settlement, located in southwestern Uganda, Isingiro District. Nakivale is the second-largest refugee camp in Uganda, hosting over 216,000 individuals spread across 79 villages [40, 41]. The inhabitants face significant challenges due to extreme weather patterns, including heatwaves and arid land during dry periods, as well as devastating floods that damage homes and agricultural production during the rainy season [9]. The camp also grapples with numerous agricultural obstacles, including a lack of livestock and restricted access to diverse crops and agricultural training [42]. Food insecurity and mental health issues are major concerns, with high rates of malnutrition among women and children, limited dietary diversity, a strong dependence on external food aid [42] and a substantial proportion of the population suffering from conditions such as generalized anxiety disorders, posttraumatic stress disorder and major depressive disorder [43]. These conditions make Nakivale a particularly relevant setting to study the interplay between climate resilience, food security and mental health.

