#### Enhanced usual care

All enrolled participants will receive EUC, which consists of a single 15-min psychoeducation session with a trained assistant overseen by a qualified mental health professional, delivered before the start of the other interventions. The session is guided by a predetermined script, addressing the issue of overthinking and offering self-management techniques [46]. Participants will also receive information on utilizing existing mental health services and UNHCR partner organizations that provide psycho-social support within the refugee settlement, as well as information about a network of trained community health workers offering basic psychosocial support.

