#### Home gardening intervention

The HGI is designed to promote climate-smart farming techniques, empowering participants to achieve greater self-sufficiency [24]. The intervention provides training on growing nutrient-dense crops on small plots near participants’ homes, emphasizing year-round cultivation, sustainable farming practices and knowledge transfer [47]. The HGI utilizes a four-pronged strategy: (1) supplying tools, seeds, and other essential materials; (2) offering education on home-based sustainable agricultural practices; (3) providing lessons on nutrition and cooking; and (4) teaching sustainable harvesting and market strategies.

The program starts with a 3-day training of trainers (ToT) for 20 model farmers and the monitoring team, led by senior trainers specializing in sustainable agriculture. Village-level training of the participants includes three in-person sessions with senior trainers at model farmers’ plots, each lasting approximately 6 h, with at least 2 h devoted to hands-on practice. The timing of these sessions will be staggered across the three strata. Thereafter, trained model farmers located in each village will provide continual support to participants throughout the intervention period. Each participant will receive regular in-person visits at their home garden from a model farmer or assistant monitor.

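### LOCF among 'completers' is not assured to be conservative, and the plan does not say whether it governs the primary 12-month analysis

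*Protocol article*

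**What the plan says.** Section {20c} opens with the analysis set: "The primary analysis will be based on an intention-to-treat (ITT) approach". It adds a per-protocol analysis as secondary and then gives two missing-data rules. The first is "Missing data will be handled using imputation estimation methods (maximum likelihood, K-Nearest Neighbors) estimation if missing at random". The second is "We will utilize a conservative last-observation-carried-forward (LOCF) approach for missing follow-up data among completers". The section does not rank the rules or link either one to a particular analysis.

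The term 'completers' is not defined. The nearest wording is the per-protocol set in Statistical methods {20a}, "including only participants who completed the allocated intervention as planned".

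The primary outcome (Outcomes {12}) is the change in FIES from baseline to 12 months. Visits are at baseline, 3 months and 12 months. Child height-for-age (HAZ) is measured only at baseline and 12 months. The sample size section {14} states: "The calculation also assumes a conservative 20% attrition rate at the 12-month follow-up". Section {20a} already plans a model with random effects for village and for repeated measures within participants.

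**The concern.** Calling LOCF conservative presumes that it can only pull the treatment contrast towards zero. That is not assured. A carried value reflects an earlier stage of the effect and an earlier point in any time trend, so the contrast can move either way. For HAZ there is no 3-month value to carry, so LOCF sets the child's change to exactly zero.

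Tying the rule to completers adds a second difficulty. If the word means those who completed their allocated intervention, the rule depends on a post-randomisation status that is probably reached by different shares of each arm. The control condition "consists of a single 15-min psychoeducation session with a trained assistant"; HGI involves "three in-person sessions with senior trainers at model farmers’ plots, each lasting approximately 6 h"; the combined arm has those three sessions and five SH+ sessions. If the word means study completers, they have a 12-month value and the rule is nearly empty for the primary endpoint.

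LOCF and ordinary K-Nearest Neighbors are also single imputations. They treat filled-in values as observed and so understate uncertainty. With the rules unranked, the handling of a missing 12-month FIES value could be chosen after the data are seen.

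**Working it through.** **Inputs from the protocol.** 30 villages allocated 1:1:1, so J = 20 per pairwise contrast with P = 0.5; 30 dyads per village, or 24 after 20% attrition; ICC 0.01; variance explained 0.50 (individual level) and 0.20 (cluster level); two-sided alpha 0.05; target difference 0.291 SD with 95% power. I take df = J − 3 = 17.

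**Reproducing the plan's figure.**

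- SE² = ICC(1 − 0.20)/(P(1 − P)J) + (1 − ICC)(1 − 0.50)/(P(1 − P)Jn).
- With n = 24: 0.008/5 + 0.495/120 = 0.001600 + 0.004125 = 0.005725, so SE = 0.0757.
- Detectable difference = (2.110 + 1.740) × 0.0757 = 0.291 SD. Power at 0.291 from the noncentral t is 0.952. Both agree with the plan.

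**SE after LOCF.** Filled-in values count as observed, so n returns to 30: SE² = 0.001600 + 0.495/150 = 0.004900 and SE = 0.070. The rejection rates below use this value.

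**A. True effect 0.291 SD, 20% missing in both arms, all carried forward.** This is an upper bound, because the rule covers completers only. Let θ be the effect in the carried value relative to the 12-month effect. Expected contrast = 0.8 × 0.291 + 0.2 × θ × 0.291.

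| θ | Expected contrast (SD) | Direction |
|---|---|---|
| 0 (no effect yet) | 0.233 | towards null; power about 88% |
| 0.5 | 0.262 | towards null; power about 94% |
| 1 | 0.291 | no bias |
| 1.5 (effect fades after month 3) | 0.320 | away from null |

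**B. No true effect, unequal missingness, all missing values carried forward from baseline.** Spurious contrast = (difference in share missing) × (time drift). The protocol gives neither quantity, so both are assumptions. The sign follows the drift and which arm loses more.

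| Missing by arm | Drift (SD) | Spurious contrast (SD) | Rejection |
|---|---|---|---|
| 20% and 20% | 0.5 | 0 | 5% |
| 25% and 15% | 0.5 | 0.10 × 0.5 = 0.05 | about 10% |
| 30% and 10% | 0.5 | 0.20 × 0.5 = 0.10 | about 27% |
| any | 0 | 0 | 5% |

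**C. No true effect, 20% missing in both arms, LOCF for intervention completers only.** The remaining missing values are taken as handled without bias. Spurious contrast = 0.20 × (difference in completer share among the missing) × drift. Completer shares and drift are assumptions.

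- 100% against 70%, drift 0.5 SD: 0.20 × 0.30 × 0.5 = 0.03 SD, rejection about 7%.
- 100% against 50%, drift 0.5 SD: 0.20 × 0.50 × 0.5 = 0.05 SD, rejection about 10%.
- Equal shares, or no drift: zero.

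**The case against.** The best defence is that the harm is conditional and the text is less committed than it looks. Most of that stands, and it limits several inferences a reader might draw.

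- *LOCF biases the primary contrast.* It can. Size and sign depend on the course of the effect, the time trend and who is missing, and the bias can be zero.
- *Missing data are handled differently by arm.* The written rule is the same for all arms. Its reach differs only if completers means intervention completers and their share differs.
- *LOCF is the primary analysis, or breaks intention-to-treat.* The section does not assign it there, and the per-protocol set is itself defined by completion, so LOCF may have been meant for that analysis. The section does not exclude the primary analysis either. Carrying values forward to retain randomised mothers is not in itself a departure from intention-to-treat.
- *The carried value comes from another season.* The setting section describes "heatwaves and arid land during dry periods, as well as devastating floods that damage homes and agricultural production during the rainy season", which makes drift plausible for a 3-month value standing in nine months later. A baseline value may lie about a year before the endpoint, so a different season is not established for it. No seasonal change in FIES is given.
- *Three incompatible rules cover the same values.* Maximum likelihood and K-Nearest Neighbors are alternatives under missing at random, and LOCF has its own stated scope. They overlap and are unranked, which is less than incompatible.
- *Power falls to 83%.* That figure uses the SE for 24 per village, removing the missing mothers after their values have been filled in. With 30 per village it is about 88%.

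The likelihood approach is also largely present already, through the model in {20a}. None of this supports the word conservative, defines completers, or says which rule governs the primary analysis.

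**Conclusion.** The point holds as a should-fix. The protocol states a method and a justification for it; this is more than detail left to an analysis plan. The justification is not assured, the group it applies to is undefined, and its place relative to the primary analysis is open.

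The 0.233 to 0.320 SD range for a true 0.291 SD rests on carrying forward the full 20% and on θ between 0 and 1.5. On the intervention-completer reading, the assumed shares and drift in scenario C give a null bias of 0.03 to 0.05 SD, with rejection of about 7% to 10%. The figure of about 27% needs a 30% against 10% split and a 0.5 SD drift, neither of which has a source in the protocol. The calculations show that the rule is not reliably conservative; they do not forecast the trial's bias.

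**What to change.** In {20c}, name the repeated-measures mixed model of {20a}, fitted by maximum likelihood under missing at random, as the single primary missing-data method for the intention-to-treat analysis. State that it includes all randomised mothers, also those with baseline only, and applies alike in every arm regardless of intervention completion.

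Delete the word conservative and the restriction to completers, and drop K-Nearest Neighbors as a primary method. Keep LOCF at most as a labelled sensitivity analysis. Multiple imputation that respects village clustering, with a delta shift for missing 12-month FIES, would be a better choice for that role.

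The cost is two sentences and slightly more analysis work. According to Trial status, baseline data were still being collected when the manuscript was submitted, so at that point the change would have preceded any follow-up data.
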